### Exclusion criteria during the follow-up periods

Patients who should not be enrolled but have been enrolled should be excluded. Patients who have received at least one dose of salvianolate or matching placebo but fail to complete the trial because of poor compliance or voluntary withdrawal should not be removed. Every withdrawal will be recorded in the case report forms (CRFs), and a visit will be arranged if possible. Although their data cannot be used for efficacy analysis, they can be used for safety analysis. The trial could be terminated in advance by investigators if there are any safety problems. Once it is terminated, all CRFs should be kept for future reference.

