## Statistical considerations

### Sample size

We use the URL (https://www.cnstat.org/samplesize/5/) to generate the calculated sample size. According to our pre-experimental results, we assume *α* = 0.05, 1-*β* = 0.80, Mean_*t*_ = 20, Mean_*c*_ = 40, *σ* = *S*_*t*_ = *S*_*c*_ = 20, *N*_t_:*N*_c_ = 1:1, and suppose that a 20% IMR reduction (Δ = − 8) is considered of clinically meaningful difference. We get approximately 36 (between 35 and 36) needed patients in each group. Considering the loss rate of 10%, the total sample size will be 78 cases with 39 cases in each group. The equation being used to estimate the sample size is as follows:
$$ n=\frac{2{\left({Z}_{\alpha }+{Z}_{\beta}\right)}^2{\sigma}^2}{{\left({\mathrm{Mean}}_t-{\mathrm{Mean}}_c-\Delta \right)}^2}. $$

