Premature discontinuation of salvianolate, loss to follow-up, and death are possible intercurrent events. As we use treatment policy strategy in our study, we will take a per-protocol analysis, as well as intention-to-treat (ITT) analysis for statistical analysis. Per-protocol analysis includes participants who complete the assigned therapy according to the trial protocol while ITT analysis includes all randomly assigned participants according to the treatment group to which they were originally assigned, regardless of the occurrence of intercurrent events. The ITT analysis will indicate how salvianolate will work in a more real-life setting. If there is evidence that the difference in the treatment depends on certain patient characteristics identified in the baseline assessment, a subgroup analysis will be performed.

The missing data before the intercurrent events will be filled with the measured values of “similar participants.” The similar patients should have the same sex and smoking history (smoker or nonsmoker). Missing values will be imputed by expectation-maximization algorithm through age, systolic blood pressure, diastolic blood pressure, fasting blood glucose, and IMR. Multiple imputation will be used in our study. *P*-value < 0.05 will be considered to indicate statistical significance. All statistical analyses will be performed using the Statistic Package for Social Science (SPSS) software package, version 18.0 (SPSS Inc., Chicago, IL, USA). The results will be published by the chief investigator and major contributors.

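### The ITT analysis keeps every randomised patient whatever intercurrent event occurs, but the fill-in rule reaches only data missing before such an event, and another section bars non-completers from efficacy

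*Protocol article*

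**What the plan says.** All but two of these statements stand in the *Analysis* part of the protocol article's statistical considerations.

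- Intercurrent events: "Premature discontinuation of salvianolate, loss to follow-up, and death are possible intercurrent events".
- Strategy: "As we use treatment policy strategy in our study, we will take a per-protocol analysis, as well as intention-to-treat (ITT) analysis for statistical analysis". The ITT set is everyone randomised, "according to the treatment group to which they were originally assigned, regardless of the occurrence of intercurrent events".
- First imputation sentence: "The missing data before the intercurrent events will be filled with the measured values of" other patients of the same sex and smoking history.
- Second: "Missing values will be imputed by expectation-maximization algorithm through age, systolic blood pressure, diastolic blood pressure, fasting blood glucose, and IMR".
- Third: "Multiple imputation will be used in our study".

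Neither the second nor the third sentence has a time limit, and the article does not say how the three fit together.

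*Exclusion criteria during the follow-up periods* deals with "Patients who have received at least one dose of salvianolate or matching placebo but fail to complete the trial" through poor compliance or voluntary withdrawal. They are not to be removed, but their data may serve the safety analysis only, not efficacy.

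*Sample size* states: "Considering the loss rate of 10%, the total sample size will be 78 cases with 39 cases in each group".

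**The concern.** Under treatment policy, the values that matter are those at Day 7 whether or not the patient stopped the infusion. For a patient who stopped, these lie after the event. A rule that fills only what is missing before the event covers the less relevant part of the gap.

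Listing loss to follow-up as an intercurrent event makes this sharper. Loss is a reason why data are missing. Once it counts as the event, every value missing because of it falls after the event by construction.

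The exclusion section then withholds efficacy data from patients who withdraw, even where a Day 7 value was obtained.

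At stake is whether the analysis labelled ITT is really a completer analysis for the Seattle angina scale, the quality of life scale, Holter monitoring and the 6-minute walk test.

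A lesser defect is that the stopping event names salvianolate alone. In a double-blind trial the event should be defined identically for both infusions.

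**Working it through.** **1. The plan's own figure.** Inputs from *Sample size*: α = 0.05, power 0.80, SD 20, means 20 and 40, Δ = −8. The denominator difference is |20 − 40 + 8| = 12. With a one-sided Z_α, the printed formula gives n = 2 × (1.645 + 0.842)² × 20² / 12² = 34.35, so 35 per group. Then 35/0.9 = 38.9, so 39 per group and 78 in total. The stated total is reproduced and is taken as given here.

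**2. How many patients depend on the unclear rule.** 39 × 0.10 = 3.9, about 4 per arm; 78 × 0.10 = 7.8, about 8 in total. The 10% is the plan's figure; the equal split between arms is an assumption.

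**3. Two readings of the imputation sentences.**

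- *One procedure.* The first sentence sets the scope and the next two say how it is carried out. The time limit then governs all of it.
- *Separate rules.* Donor matching covers values missing before the event; the other two sentences cover all missing values. Values missing before the event then fall under several methods with no order between them, and the limit does no clear work.

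**4. Typical patients set against these readings.**

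- *Stops the infusion, Day 7 value obtained.* Treatment policy and the ITT definition use the value. The exclusion section bars it if the reason was poor compliance or voluntary withdrawal.
- *Stops salvianolate, Day 7 value missing.* Not filled on the first reading; filled on the second.
- *Lost to follow-up, either arm.* Not filled on the first reading; filled on the second.
- *Died before Day 7, either arm.* Treatment policy supplies no value, so deaths need their own report.
- *Stops placebo, not lost, alive, Day 7 value missing.* On the literal wording no intercurrent event has occurred, so the time limit does not apply. The documents give no rate for this narrow group.

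**5. Which end points.** *End points* and Table 2 put the primary IMR comparison on Day 1, after the first 30-minute infusion. Events later in the 7-day course cannot cause that value to be missing. The exposed end points are those collected at Day 7. The exclusion sentence does not distinguish end points, which is one more reason to limit its scope.

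**The case against.** The strongest reply is that imputation as a whole is not restricted. Two of the three sentences have no time limit, so values missing after an event may well be covered. That stands as a possible reading, and it rules out saying flatly that patients who stop or are lost are not imputed. It does not rescue the text, because it leaves the limit without a purpose and the choice of rule to the analyst.

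A second reply is that this is a condensed article and missing-data detail belongs in an analysis plan that is not shown. This is fair for details left out. The point here is a stated limit and a stated exclusion that conflict with a stated strategy.

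A reader might go further and infer that the arms follow different rules, in salvianolate's favour. The documents do not support this:

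- Loss and death are also listed and apply to both arms. The ITT definition covers both groups, and the exclusion section names salvianolate and placebo together. Only one phrase is arm-specific.
- The size one might attach to such a bias does not measure it. Suppose a fraction p of the salvianolate arm is omitted and would score D standard deviations worse than completers. That arm's mean then shifts by p × D. With p = 0.10 and D = 1, the shift is 0.10 SD. Against a standard error of √(1/35 + 1/39) = 0.233 SD, this is 0.43 standard errors. With p = 0.20, it is 0.20/√(1/31 + 1/39) = 0.20/0.241 = 0.83.
- The arithmetic is right, but it gives the shift in one arm's mean. D and the 20% are assumptions. The plan's 10% loss applies to both arms, and with equal p and D, omission in both arms cancels: 0.10 × D − 0.10 × D = 0. Placebo values borrowed from matched patients with observed data would also sit near completer values, so the placebo mean would shift in much the same way.

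**Conclusion.** The concern holds in a limited form. The treatment-policy ITT statement conflicts with the time limit on the fill-in, with the listing of loss as an intercurrent event, and with the bar on using non-completers' efficacy data. The stopping event also needs to name both infusions.

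On one reading of the imputation sentences, Day 7 values missing after stopping or loss stay unfilled; on the other, the rule is ambiguous. Either way the text needs correcting.

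About 4 of 39 patients per arm are concerned, given the plan's 10% loss and an equal split. The effect is on the Day 7 secondary end points, with the primary end point largely unaffected. Neither arm-specific rules nor a direction of bias is established, so no figure for bias in the treatment difference is claimed. The correction should be made because the conflict is in the text and is cheap to remove.

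**What to change.** In *Analysis*:

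- (a) Define the stopping event as premature discontinuation of the assigned infusion, salvianolate or placebo.
- (b) Take loss to follow-up out of the intercurrent events and handle it as missing data.
- (c) Delete the restriction to data missing before an intercurrent event. Apply one multiple-imputation rule, the same in both arms, to every missing Day 7 value of randomised patients alive at Day 7. Where a value was observed after stopping, use it.
- (d) Report deaths separately.

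In *Exclusion criteria during the follow-up periods*, limit the exclusion of non-completers from efficacy to the per-protocol analysis, so that it agrees with the ITT definition. Changing *Analysis* alone would leave that contradiction in place.

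The cost is a few sentences, a little more analysis work and possibly slightly wider intervals. No patients or procedures are added.

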## Discussion

Traditional methods for improving angina include drug therapy, interventional therapy, and coronary artery bypass grafting. However, up to 49% of patients with angina have no significant coronary artery stenosis [20, 21]. Among them, 50 to 65% of patients have impaired coronary vasodilatation, resulting in coronary microcirculatory disturbances [1]. The European Society of Cardiology 2013 guideline for stable CHD clearly incorporates coronary microcirculatory disorder into the field of stable CHD and proposes the concept of CHD patients with ischemic symptoms but no evidence of obstruction [22]. Their risk of long-term cardiovascular events (mortality, hospitalization for acute coronary syndrome and stroke) is comparable to obstructive coronary disease [23, 24]. The tiny blood vessels of the coronary circulation mainly nourish the myocardium and cardiac autonomic nerves and play a crucial role in the regulation of myocardial metabolism [25]. Even in the absence of obstruction of the epicardial coronary artery, microvascular contraction and relaxation can also regulate coronary blood flow and myocardial perfusion, directly affecting cardiac function.

Risk factors for CHD such as smoking, old age, hyperlipidemia, diabetes, and mental stimulation can damage small coronary endothelium cells and affect coronary microcirculation [26]. Endothelial and smooth muscle dysfunction, sympathetic nerve dysfunction, microvascular atherosclerosis, and inflammation are closely related to microcirculation disorders [27]. The treatment of coronary microcirculation disorders can only rely on drugs, but currently, there is no clear and effective treatment of drugs. Salviae miltiorrhizae is a traditional Chinese herb and its effective ingredient salvianolate can protect the cardiovascular system at cellular levels [12]. It can inhibit the production of reactive oxygen species and increase the antioxidant capacity of cardiomyocytes [28], as well as improve microvascular reflow by inhibiting oxidative stress and apoptosis [16]. Previous study has demonstrated that five salviae miltiorrhizae-based preparations, including salvianolate injection, were effective in the treatment of stable angina pectoris with clinical improvement rate of 72.4 to 91.6% and electrocardiography improvement rate of 54.5 to 71.6% [29]. However, the effect of salvianolate intravenous infusion on the myocardial IMR in patients with high FFR and myocardial microcirculatory disturbance remains unclear. Accordingly, we focus on this issue and further explore the improvement effect of salvianolate on angina symptoms and myocardial ischemia.

Nonetheless, there are still limitations in this study. First, this study is a single-center participation study. Second, salvianolate will be compared with placebo only in this study, and there are no other comparative groups for effective drugs for coronary microcirculatory disturbances, such as angiotensin-converting enzyme inhibitors. Other non-inferiority and superiority trials may be needed. Although the study could only be designed based on the aforementioned limitations, we can still evaluate the effect of intravenous salvianolate infusion on IMR in stable CHD patients with high FFR and myocardial microcirculatory disturbance and test the improvement of the clinical symptoms of CHD patients with stable microcirculatory disturbance.

In conclusion, this study will clarify the effect of salvianolate on coronary microcirculation and provide an effective treatment for patients with stable CHD with high FFR and myocardial microcirculatory disturbances.

### Trial status

Chinese Clinical Trial Registry ChiCTR1800018772, version 2. Registered on 9 October 2018 and last updated on 2 March 2020. Participant recruitment began in January 2020 and is expected to continue until 2022. Randomization of the participants was performed on the same day.

## Data Availability

Not applicable.

## Abbreviations

IMR: Index of microcirculatory resistance
FFR: Fractional flow reserve
CHD: Coronary heart disease
CRFs: Case report forms
CBC: Complete blood count
K: Potassium
Na: Sodium
Cl: Chloride
ALT: Alanine aminotransferase
AST: Aspartate aminotransferase
BIL: Bilirubin
Scr: Serum creatinine
BUN: Blood urea nitrogen
UA: Uric acid
cTnT/cTnI: Cardiac troponin T/I
SD: Standard deviation
ITT: Intention-to-treat
SPSS: Statistic Package for Social Science
